### Outcome measures

#### Mother

Primary outcome of this trial is (cumulative) incidence of relapse or recurrence of a depressive episode (as defined by the SCID-I [36]) during pregnancy and up to 12 weeks postpartum. The SCID-I is assessed at baseline (T0) and 12 weeks postpartum (T6). If – based on assessment with the HDRS at fixed time-points – relapse/recurrence is suspected, the SCID-I will be performed intermittently.

For registration of severity of depressive symptoms, the HDRS will telephonically be assessed additionally, at baseline (T0), at 36 weeks of gestation (T3), and 12 weeks postpartum (T6), and also intermittently, if necessary [37]. When the HDRS at any stage turn out above cut-off scores, the participant will be called one week after initial measurement. The HDRS will be repeated to confirm or reject elevated scores. An adjusted telephonic version of the everyday problem checklist (EPCL) and pregnancy related life events will be assessed during each telephonic measurement (T0, T2, T3, T5 and T6).

Women will be asked to fill in questionnaires during five occasions: baseline (T1), 24 and 36 weeks of gestation (T2 and T3), and 4 and 12 weeks postpartum (T5 and T6). The questionnaires differ in composition at the five measurement moments, as shown in Table 1. During these occasions, participants are variably asked to report on anxiety symptoms (Dutch version of the State Trait Anxiety Inventory STAI), short and long version [49, 50]), depressive symptoms (the Dutch version of the Edinburgh Postnatal Depressions Scale; EPDS [51]), childhood trauma (Childhood Trauma Questionnaire; CTQ [52]), affect (the International Short-Form of the Positive and Negative Affect Schedule; I-PANAS-SF [53]), dysfunctional attitudes (Dysfunctional Attitude Scale; DAS [54]), medication beliefs (Beliefs about Medicines Questionnaire; BMQ [55]), medication adherence (Medication Adherence Rating Scale; MARS [56]) and Quality of Life (EQ-5D-5L [57]). Socioeconomic position, ethnicity, smoking behaviour, alcohol use, family history and information on previous pregnancies and family size will be assessed using the Mind2Care questionnaire [58], a screen-and-advice instrument to detect mental health problems among pregnant women.

**Table 1 Tab1:** Assessment per measurement moment

	Method	T0	T1	T2	T3	T4	T5	T6	T7
Clinical Diagnostic Interview (SCID-I)	Int	X		…	…	…	…	X	
Depressive symptoms (HDRS)	Int	X		…	X	…	…	X	
Peripartum depression (EPDS)	SR		X	X	X		X	X	

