### Sample size

Sample size calculation is based on the main aim of this study, which is to demonstrate non-inferiority of preventive CT with guided discontinuation of SSRIs (STOP) compared to continuation (GO), with respect to relapse or recurrence of a depressive episode up to 3 months postnatal. We will use a non-inferiority margin (tolerance threshold, ‘delta’) of 15 %. This is based on the assumption that this excess relapse (taking into account the possibility of restoring SSRI treatment) is still in balance with the expected beneficial effects of discontinuation of SSRI for the remaining mothers. We also anticipate that this balance is acceptable for women.

With this non-inferiority margin, and the assumption that the overall absolute risk of relapse will be around 15 % [67], we need 178 women, given alpha .025, power 80 %, and a one-sided test. To account for some attrition, we aim to include 200 women in total. Given this sample size, we have sufficient power to demonstrate small to moderate effect sizes of .42 or over on continuous secondary outcomes. With respect to dichotomous secondary outcomes, we will be able to detect odds ratios of 1.5 or over when the base probability is .5.

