### Statistical analysis

Analysis will primarily be carried out according to the intention-to-treat principle, i.e., the participants will be analysed according to their randomized allocation, regardless of the actual interventions received by the participant. Supplementary, we will perform analyses per protocol, i.e., according to actual SSRI use, irrespective of randomized arm.

The primary outcome, risk (cumulative incidence up to 3 months postnatal) of relapse of depression, will be compared between the randomized groups. Differences will be assessed statistically using a one-sided Chi-Square Test at a significance level of .025 and will be presented as a risk difference. The remainder of statistical tests will be performed two-sided at a significance level of .05.

Time to relapse will be compared between the randomized groups using survival analysis. Kaplan-Meier curves will be constructed and differences will be tested using the log-rank test. A Cox proportional hazard model will be used to calculate hazard ratios

Continuous outcomes, e.g., the General Movements scores at 3 months, will be compared between the groups using the unpaired *t*-test. Categorical secondary outcomes, e.g., obstetric complications, will be tested using Chi-Square Tests. For the continuous variables and categorical variables that are assessed more than twice, we will deploy linear mixed models and generalized linear mixed models respectively. These models use all available data (do not exclude persons with missing values) under the assumption of data being missing at random, and account for within-subject correlation over time. If despite randomization prognostically important factors differ between the groups, they will be adjusted for in supplemental analyses by including these factors in the pertaining regression models.

Subgroup analyses will be undertaken according to: Dutch/non-Dutch, nulliparous/multiparous, yes/no history depressive disorder and/or anxiety disorder, yes/no co-morbid anxiety symptoms or disorder. All effect parameters will be supplied with a 95 % confidence interval.

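### The main analyses of repeated secondary outcomes plan no adjustment for the outcome's own baseline score, although it is collected; prespecifying that adjustment would cost nothing and sharpen the estimates

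*Protocol article*

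**What the plan says.** The Statistical analysis section of the protocol article compares continuous outcomes by unpaired t-test and repeated ones by mixed model: "For the continuous variables and categorical variables that are assessed more than twice, we will deploy linear mixed models", with the generalized form for the categorical ones. On the data entering these models it says: "These models use all available data (do not exclude persons with missing values) under the assumption of data being missing at random". Its only rule on covariates concerns prognostically important factors that differ between the arms despite randomization: "they will be adjusted for in supplemental analyses by including these factors in the pertaining regression models".

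The schedule is in the Mother section and Table 1. The HDRS is taken "at baseline (T0), at 36 weeks of gestation (T3), and 12 weeks postpartum (T6"), and in between if needed. The questionnaires are described thus: "Women will be asked to fill in questionnaires during five occasions: baseline (T1), 24 and 36 weeks of gestation (T2 and T3"), followed by two postpartum occasions (T5 and T6). Table 1 has EPDS, STAI, I-PANAS-SF and EQ-5D-5L on all five questionnaire occasions, DAS at T1, T2 and T3, and hair cortisol at T1, T4 and T6.

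The Sample size section claims power for "small to moderate effect sizes of .42 or over on continuous secondary outcomes".

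**The concern.** An outcome's own baseline score is usually among the best predictors of its later values. Adjusting for it reduces residual variance whether or not the arms happen to differ at baseline. The stated rule ties adjustment to observed imbalance and places it in supplemental analyses, so the main comparisons forgo that gain.

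This holds however the occasions are counted. HDRS, DAS and hair cortisol each have one baseline and two later scheduled values. If baseline counts, they go to a mixed model for which no baseline adjustment is stated. If it does not count, they fall back to the unpaired t-test, which has no covariate.

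At stake is the precision of the secondary comparisons of depressive severity, anxiety, affect, attitudes, quality of life and cortisol. These are tested for difference, so avoidable imprecision makes an effect of tapering, in either direction, harder to see.

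**Working it through.** **Inputs.** 178 evaluable women at 1:1 allocation, i.e. 89 per arm; 80 % power; two-sided .05 for secondary tests; detectable effect .42 (Sample size, Randomisation and Statistical analysis sections). Occasions after baseline: k = 4 (EPDS, STAI, I-PANAS-SF, EQ-5D-5L) or k = 2 (HDRS, DAS, hair cortisol). The correlation rho between occasions is not given; I assume .3, .5 and .7. SD is 1, data are complete, and the correlation is compound symmetric unless stated. The results apply to the linear models.

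**1. The plan's own figure.** (1.96 + 0.84) × √(2/89) = 2.80 × .150 = .42. It reproduces as a single-occasion, unadjusted comparison.

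**2. Single follow-up with baseline adjustment.** Variance falls by rho² (9 %, 25 %, 49 %), so the detectable effect is .42 × √(1 − rho²):
- rho .3: .40
- rho .5: .36
- rho .7: .30

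**3. Mean of k follow-ups, unconstrained arm-by-time model against baseline adjustment.** The variance factor for the post-baseline contrast is (1 + (k − 1)rho)/k. Adjustment subtracts rho². SE = √(2/89 × factor). At rho .5:
- k = 4: factors .625 and .375; SE .119 against .092; ratio √(.625/.375) = 1.29.
- k = 2: factors .750 and .500; SE .130 against .106; ratio √(.750/.500) = 1.22.

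The change-from-baseline contrast from the same unconstrained model has factor (1 + (k − 1)rho)/k + 1 − 2rho, which at rho .5 gives the same SEs. Keeping baseline as a response with equal arm means gives the same SEs as covariate adjustment (.092 and .106).

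**4. Sensitivity to rho.** SE of each unconstrained contrast divided by the adjusted SE:
- k = 4, rho .3: post-only .1033/.0930 = 1.11; change .1402/.0930 = 1.51.
- k = 4, rho .7: post-only .1320/.0800 = 1.65; change .0918/.0800 = 1.15.
- k = 2, rho .3: post-only .1209/.1122 = 1.08; change .1536/.1122 = 1.37.
- k = 2, rho .7: post-only .1382/.0899 = 1.54; change .1006/.0899 = 1.12.

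The excess thus runs from 11 % to 65 % with five occasions and from 8 % to 54 % with three.

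Under AR(1) with rho .5, the post-only ratios are .1076/.1017 = 1.06 (k = 4) and .1298/.1170 = 1.11 (k = 2). The change ratios are .1534/.1017 = 1.51 and .1499/.1170 = 1.28.

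**5. Only if one common arm effect spans all occasions including baseline.** A constant effect is multiplied by k/(k + 1) under compound symmetry, whatever rho is:
- k = 4: .42 × 4/5 = .336, a dilution of 20 %.
- k = 2: .42 × 2/3 = .280, a dilution of 33 %.

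Under AR(1), rho .3 to .7, the estimates are .318 to .275 (24 % to 35 %) and .264 to .237 (37 % to 44 %).

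**6. Against the promised .42.** The unconstrained model at rho .5 detects 2.80 × .119 = .33 (five occasions) or 2.80 × .130 = .36 (three). Both are better than promised, so the loss is measured against what the collected data allow, not against the plan's claim.

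**The case against.** The strongest reply is that the article leaves the fixed effects, the role of baseline and the arm contrast open, and that a journal article may leave these to the analysis plan. Much of this stands. A reader might infer from the occasion-counting rule that baseline is treated as one more outcome occasion and the arm effect thereby diluted. The text does not support that: baseline plus two follow-ups is also the smallest schedule that needs a mixed model when baseline is a covariate. The HDRS may also be repeated between fixed visits. Dilution requires one common effect spanning baseline, and precision loss requires an unconstrained model; the article selects neither. A constrained model with baseline as a response loses nothing and is compatible with the wording.

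Three further points stand:
- Non-inferiority rests on relapse risk, and all effects carry 95 % confidence intervals, so imprecision would be visible.
- A reader might infer that a chance baseline difference in EQ-5D-5L feeds into the QALY result. The Economic evaluation section gives no QALY estimator, so that cannot be claimed.
- The pre-assessment interview (T0) precedes randomization, but the text does not show that the T1 questionnaires are completed before allocation is known.

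The reply does not remove the covariate rule. That rule is stated, not left open: it makes adjustment supplemental and conditional on imbalance. An analysis plan that followed it would carry it forward.

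**Conclusion.** The point holds as a cost-free improvement to secondary analyses. As written, no main comparison of a repeated secondary outcome plans adjustment for its own baseline score. If the mixed model is an unconstrained arm-by-time model, estimates are unbiased but standard errors are about 22 % to 29 % larger than needed at an assumed rho of .5 under compound symmetry, with the wider range shown above for other correlations. Dilution by 20 % or 33 % arises only under a common arm effect that includes baseline, which the article does not state.

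The figures rest on an assumed correlation, complete data and a constant effect at every follow-up. Women enter in remission, so the correlation with baseline may be low for symptom scores and the gain correspondingly small. The primary outcome, the 178 women and the stated .42 are untouched.

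**What to change.** State in the Statistical analysis section that the main mixed models estimate the arm difference at post-randomization occasions only. Then choose one form in advance: the outcome's own baseline value as a prespecified covariate, or baseline kept as a response with equal arm means at baseline. Apply it whatever the observed imbalance, so that own-baseline adjustment leaves the supplemental rule. That rule can remain for other prognostic factors.

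Use T0 for the HDRS. For measures first taken at T1 (EPDS, STAI, I-PANAS-SF, DAS, EQ-5D-5L, hair cortisol), first confirm that T1 was obtained before the woman knew her allocation.

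The cost is wording only: the baseline values are already collected, and no sample size or visit changes. The equal-means form also retains women whose baseline score is missing. The wording should be fixed before outcome data are seen by arm.

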### Randomisation

Two hundred women will be randomized in a 1:1 allocation ratio to either the intervention arm (STOP) or the care as usual arm (GO). Randomization will be done with a web based computer-generated randomization schedule (a validated TENALEA Clinical Trial Data Management System; http://www.formsvision.com/) using permuted blocks of random size with a maximum of 16 and stratified for the number of previous depressive episodes (dichotomized). Based on a recent review [35], the participants are divided into groups of participants with 3 or less previous depressive episodes, versus 4 or more. Allocation of participants is concealed for study researchers.

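### Randomisation is stratified by number of previous depressive episodes, but no described analysis uses that factor, and covariates enter only supplemental models, only when imbalanced; the cost in precision is small

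*Protocol article*

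**What the plan says.** Under Randomisation: "Two hundred women will be randomized in a 1:1 allocation ratio", in permuted blocks of random size up to 16. The strata are "3 or less previous depressive episodes, versus 4 or more", a cut-off taken from a cited review.

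Under Sample size: "we need 178 women, given alpha .025, power 80 %, and a one-sided test". The risk and the margin are both 15%. The target then rises to 200: "To account for some attrition, we aim to include 200 women in total".

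Under Statistical analysis, the primary outcome is compared by a one-sided chi-square test at .025 and presented as a risk difference. Time to relapse has Kaplan-Meier curves, a log-rank test and a Cox model. Other outcomes have t-tests, chi-square tests or mixed models. No strata or covariates are named for any of these. The subgroup list includes a yes/no history of depressive and/or anxiety disorder, which is not the stratification variable. Adjustment appears once: "If despite randomization prognostically important factors differ between the groups, they will be adjusted for in supplemental analyses".

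**The concern.** A factor chosen to stratify randomisation is normally one expected to predict outcome. Stratifying removes the between-stratum part of the variability from the treatment contrast. An analysis that ignores the strata still counts that part, so its standard error is somewhat larger than the design warrants. Here that widens the interval to be compared with the 15-point margin.

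The stated adjustment rule does not repair this. It acts on observed imbalance, and stratified blocks are there to prevent imbalance in this very factor. It also leaves open which factors count as prognostic and what counts as a difference. The content of the supplemental adjusted models would therefore be settled only after the baseline data are seen.

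**Working it through.** **Inputs from the article.** Relapse risk p = 0.15 in both arms, margin δ = 0.15, one-sided α = 0.025 (z = 1.960), power 80% (z = 0.8416), 178 evaluable women, 200 randomised, maximum block size 16. The non-inferiority comparison is taken as a risk difference with unpooled variance.

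**Assumed, because the article gives neither.** Share f of women with 4 or more episodes: 0.2 to 0.5. Relapse risk ratio RR between strata: 1.5 to 3.

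**1. The plan's own figure.** n per arm = (1.960 + 0.8416)² × 2 × 0.15 × 0.85 / 0.15² = 7.849 × 0.255 / 0.0225 = 88.95, so 89 per arm and 178 in total. This reproduces the stated number with no stratum or covariate term. With SE = √(2 × 0.1275 / 89) = 0.0535, power is Φ(0.15/0.0535 − 1.960) = 80.0%. With 200 evaluable it is 84.4%.

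**2. Would the imbalance rule bring the stratifier in?** Within a stratum, an unfinished block of 16 can leave one arm at most 8 women ahead. If both strata were at that limit in opposite directions, the share with 4 or more episodes would differ between two arms of 100 by 8/100, or 8 percentage points. That is the extreme, and typical differences are smaller. The rule would seldom be triggered by this factor.

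**3. Precision lost by formula.** Hold the overall risk at 15%:
- p0 = 0.15 / (1 − f + f·RR), and p1 = RR·p0
- within-stratum variance W = (1 − f)·p0(1 − p0) + f·p1(1 − p1)
- SE_u = √(2 × 0.1275/89), and SE_w = √(2W/89)
- power of the unadjusted test under stratified randomisation = Φ((0.15 − 1.960·SE_u)/SE_w)
- power of the stratified test = Φ(0.15/SE_w − 1.960)

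Example, f = 0.3 and RR = 2: p0 = 0.115, p1 = 0.231, W = 0.1247, W/0.1275 = 0.978, SE_w = 0.0529. Power is .8028 unadjusted and .8088 stratified.

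| f | RR | p0, p1 | variance ratio | N needed | power unadjusted | power stratified | gain (points) |
|---|---|---|---|---|---|---|---|
| 0.2 | 1.5 | .136, .205 | .9942 | 178 | .8009 | .8025 | 0.2 |
| 0.2 | 2 | .125, .250 | .9804 | 176 | .8025 | .8079 | 0.5 |
| 0.2 | 3 | .107, .321 | .9424 | 168 | .8072 | .8230 | 1.6 |
| 0.3 | 1.5 | .130, .196 | .9930 | 178 | .8010 | .8030 | 0.2 |
| 0.3 | 2 | .115, .231 | .9781 | 176 | .8028 | .8088 | 0.6 |
| 0.3 | 3 | .094, .281 | .9421 | 168 | .8073 | .8231 | 1.6 |
| 0.5 | 1.5 | .120, .180 | .9929 | 178 | .8010 | .8030 | 0.2 |
| 0.5 | 2 | .100, .200 | .9804 | 176 | .8025 | .8079 | 0.5 |
| 0.5 | 3 | .075, .225 | .9559 | 172 | .8055 | .8176 | 1.2 |

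By the same approximation, the one-sided level of the unadjusted test, 1 − Φ(1.960·SE_u/SE_w), is .0217 to .0247. It is slightly conservative.

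**4. Simulation check.** 200,000 replicates, 176 women (strata rounded to even sizes), Wald limits. For the error rate, each STOP stratum risk is set 15 points above GO.

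| f | RR | error unadjusted | error stratified Wald | power unadjusted | power stratified Wald |
|---|---|---|---|---|---|
| 0.3 | 1.5 | .0263 | .0273 | .796 | .807 |
| 0.3 | 2 | .0248 | .0266 | .798 | .812 |
| 0.3 | 3 | .0245 | .0283 | .803 | .826 |
| 0.5 | 2 | .0262 | .0278 | .798 | .811 |

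Simulation error on the error rates is about √(.025 × .975/200,000) = .0003. The unadjusted test stays close to .025. The simple stratified Wald test runs a little high, so part of its simulated gain of 1.1 to 2.4 points may reflect that rather than real precision.

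**The case against.** The strongest reply is that nothing here is invalid. One unadjusted intention-to-treat comparison is fixed in advance, it matches the sample size calculation exactly, and ignoring a stratifier errs, if at all, in the safe direction for a non-inferiority claim. That stands. So does the point that a condensed article may leave lists of strata and covariates to an analysis plan that is not shown. Absence from the article means only that the factor is not mentioned there. The imbalance rule is different, because it is stated text.

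Some stronger readings are tempting but unsupported:

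- *The data choose the model for the primary result.* They do not. The rule is confined to supplemental analyses.
- *The rule ignores prognosis.* It does not. Prognostic importance is one of its conditions. What is missing is the list of factors and the criterion for a difference.
- *A spurious imbalance is likely.* Ten independent factors each tested at .05 would give 1 − .95¹⁰ = 40%, but the article states neither ten factors nor a significance test of baseline differences.
- *The power loss is substantial.* With equal strata, risks of 8% and 22% give a variance ratio of .962 and power of .815. Risks of 5% and 25% give .922 and .831. Those pairs are risk ratios of 2.75 and 5, and nothing in the article supports a ratio as high as 5.
- *The stratifier is known to be prognostic.* The article says only that the division rests on a review. Prognostic value is a reasonable inference, not a stated fact.

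**Conclusion.** The point holds in a limited form. The article stratifies on number of previous episodes, describes no analysis that uses it, and states an adjustment rule that is triggered by imbalance, left undefined, and unlikely to admit that factor. The primary test is valid and prespecified, and its type I error is not materially inflated.

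Under the assumed range (RR 1.5 to 3, f 0.2 to 0.5), the cost is about 0.6 to 6% of the variance, 0.2 to 1.6 power points by formula, or 0 to 10 of the 178 women. If the stratifier is not prognostic there is no loss. The case for change rests on aligning the analysis with the randomisation and fixing the supplemental covariates in advance, at almost no cost, more than on the size of the gain.

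**What to change.** - Report the primary risk difference stratified by, or standardised over, 3 or fewer versus 4 or more episodes, with its 95% confidence interval compared with the 15-point margin. Use a variance or interval method whose error rate has been checked, since the simple stratified Wald version ran at .027 to .028. Keep the unadjusted comparison as sensitivity.
- Stratify the log-rank test and the Cox model by the same factor.
- Replace the imbalance trigger for supplemental analyses with a fixed set: the stratifier plus baseline HDRS (T0) and EPDS (T1). The article's text does not place T1 relative to randomisation, so confirm that the EPDS is completed before allocation is known.

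All these variables are already collected. The cost is a change of wording and minor extra analysis work. The return in precision is small, and the change should be made before any outcome data by arm are seen.

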### Participants

Women who are less than 16 weeks pregnant and use a SSRI primarily for depressive disorder, and are currently at least in remission or recovered [35], are invited to participate in the trial. Exclusion criteria are multiple pregnancy, as these women have a markedly increased obstetric risk, thereby threatening the homogeneity of the study population and thus potentially complicate the statistical analysis, and insufficient proficiency in Dutch or English, since our intervention is not yet available in other languages. Also, women will be excluded with severe medical conditions, such as oncology-related conditions or conditions that need urgent medical interventions, which involve treatment decisions overriding research participation. Exclusion criteria related to mental health are: current mania or hypomania or a history of bipolar illness, suicidality and serious self harm, any psychotic disorder (current and previous), current alcohol or drug misuse, predominant anxiety disorders and personality disorders that require psychotherapeutic treatment for more than 2 sessions a month.

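### As worded, the depression/anxiety history subgroup has an empty no level, because the entry criteria place every participant in the yes level

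*Protocol article*

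**What the plan says.** The Statistical analysis section of the protocol article names four subgroup factors. The list opens "Subgroup analyses will be undertaken according to: Dutch/non-Dutch, nulliparous/multiparous", continues with "yes/no history depressive disorder and/or anxiety disorder", and closes with "yes/no co-morbid anxiety symptoms or disorder". The article does not define the third item further.

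Three other sections bear on who can fall in each level of that item:

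- **Participants.** Eligible women "use a SSRI primarily for depressive disorder, and are currently at least in remission or recovered". Among the exclusions are "predominant anxiety disorders and personality disorders that require psychotherapeutic treatment" beyond a stated frequency.
- **Outcome measures, Mother.** The primary outcome is the cumulative "incidence of relapse or recurrence of a depressive episode" up to 12 weeks postpartum.
- **Randomisation.** Allocation is stratified on one factor, the number of earlier depressive episodes, cut at "3 or less previous depressive episodes, versus 4 or more". This factor is not in the subgroup list.

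**The concern.** A subgroup analysis compares the treatment effect between at least two groups, so each level of the factor must be able to contain participants. Here the entry criteria appear to put everyone in one level. If so, one of the four stated subgroup analyses returns only the overall result under another label. It is also the only listed item that addresses depression history, so the published list would hold no workable analysis of whether the STOP–GO difference varies with that history.

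The problem lies in what the article states, not in detail left to another document. The factor and its two levels are given, and they do not fit the article's own eligibility rule. An analysis plan that repeated the line would inherit the problem.

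**Working it through.** **Step 1: can the no level be filled?** This is a check of logic, not of arithmetic.

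1. Entry requires an SSRI taken mainly for depressive disorder, with the woman now in remission or recovered (Participants). Both states presuppose a past depressive disorder.
2. The primary outcome is relapse or recurrence (Outcome measures, Mother). Both terms presuppose an earlier episode.
3. The subgroup item joins depressive and anxiety disorder by and/or. Adding anxiety can only enlarge the yes level. The argument therefore does not depend on how the anxiety exclusion is read: a woman who also has an anxiety disorder is still a yes.
4. Expected split under the literal wording, barring enrolment errors: 200 yes, 0 no. The yes-level risk difference equals the overall one. The no-level risk difference and the interaction do not exist.

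**Step 2: is the main design affected?** Inputs from the Sample size section: risk 15% (taken as equal in both arms), margin 15 points, one-sided alpha 0.025, power 80%.

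n per arm = (1.960 + 0.842)² × 2 × 0.15 × 0.85 / 0.15² = 88.95, rounded up to 89, so 2 × 89 = 178.

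This reproduces the stated 178. The 200 to be enrolled allow for 1 − 178/200 = 11% attrition. Neither figure involves the subgroup factor.

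**Step 3: what would the episode-count strata deliver?** Inputs: 200 women, 1:1 allocation, 15% risk in both arms. The article gives no stratum split, so 50:50 and 70:30 are assumptions. With m women per arm in a stratum, the normal-approximation 95% half-width for the risk difference is

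1.96 × √(2 × 0.15 × 0.85 / m) = 1.96 × √(0.255 / m).

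| Assumed split | m per arm in the (smaller) stratum | Half-width in that stratum | Half-width of the interaction |
|---|---|---|---|
| 50:50 | 50 | 1.96 × √(0.255/50) = 0.140 | 1.96 × √(0.255/50 + 0.255/50) = 0.198 |
| 70:30 | 30 | 1.96 × √(0.255/30) = 0.181 | 1.96 × √(0.255/30 + 0.255/70) = 0.216 |

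If only 178 women are analysable and the split is 50:50, m = 178/4 = 44.5 and the half-width is 1.96 × √(0.255/44.5) = 0.148.

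The probability of showing non-inferiority within one stratum, when the true risks are equal, is Φ(0.15/SE − 1.96). That gives 0.556 for m = 50 and 0.37 for m = 30. Both levels can be estimated, but imprecisely.

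**The case against.** The strongest reply is that the phrase is abbreviated and may have been meant in a way that fills both levels. Three such readings are possible.

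- **History before the index episode.** The lower stratum in the Randomisation section has no stated minimum of one. If the count leaves out the index episode, zero earlier episodes is possible, and so is a no level.
- **Anxiety history alone.** This would give two groups.
- **Family history.** The Mother section says this is collected.

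Each reading needs words that the item does not contain. The first needs a reference to the index episode. The second drops the depressive disorder that the item names, and would overlap the separate co-morbid anxiety item unless the two were distinguished. The third needs the word family, which the article uses when it means that. What stands is that the count of 0 of 200 holds for the text as written and may not hold for what was intended. Either way, the line has to be rewritten.

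The reply is right on two further points. First, a reader might infer that leaving the stratification factor out of the subgroup list is itself a mistake. It is not. Stratification balances the arms, whereas subgroups explore effect modification, and no rule ties the two together. An analysis plan not shown here could also list the factor, so the article does not show that such an analysis would be post hoc. Second, a reader might infer that an episode-count subgroup would settle whether stopping is acceptable after many episodes. The article does not pose that as its question, and intervals of about ±14 to ±18 points per stratum cannot settle it against a 15-point margin.

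**Conclusion.** The point holds for the wording in the article. The history subgroup has an empty no level (0 of 200), the yes level is the whole trial, and no interaction can be estimated. This rests on the Participants criterion being applied as written and on history carrying its ordinary meaning.

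The consequence is limited to one of four subgroup analyses. The margin, the 178 women, the intention-to-treat comparison and the time-to-relapse analysis are untouched, and nothing is biased. It still merits correction before the data are seen, because choosing among the possible meanings afterwards would undo the pre-specification.

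**What to change.** Amend one item in the Statistical analysis section. Replace the history subgroup with the stratification categories, 3 or fewer versus 4 or more earlier depressive episodes. For each stratum report the STOP–GO risk difference with a 95% confidence interval, add an arm-by-stratum interaction on the same scale, and label the analysis exploratory given the widths shown above.

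If anxiety was the intended factor, write history of anxiety disorder (yes/no) instead, and state how it differs from the co-morbid anxiety subgroup. If neither was intended, define the item so that both levels can occur under the entry criteria, or delete it.

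The episode-count version needs no new data, because the variable must be known for every woman before she is randomised. It changes neither the sample size nor the primary analysis. The cost is one line of text.
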